### Data collection and monitoring

After completing the assigned intervention, participants will be contacted by the designated researcher responsible for monitoring and managing the evaluation processes. They will receive a link to an online survey to complete the post-treatment assessment and follow-up (at three months post-intervention). Throughout the study, there will be careful monitoring for any potential adverse effects experienced by participants although, owing to the nature of the intervention programs, such effects are not expected to occur [34]. Participants will be encouraged to promptly report any signs of worsening during sessions. However, should any adverse effects arise, the psychotherapist overseeing the intervention will report them to an independent data monitoring committee (IDMC) that is not directly involved in the study being monitored. This committee will comprise a biostatistician, a clinical psychologist, and a psychiatrist. They will assess the situation and determine if any additional measures are necessary to ensure the participant’s safety, such as referral to a hospital service, and the scientific integrity of the study. The anticipated RCT flowchart of participants in the study is provided as Fig. 1.

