### Randomization, allocation, and blinding

A research assistant will be responsible for assigning a unique code to each participant and communicating it via email. This research assistant will be the sole person with access to participants’ personal data, along with their respective codes and the group to which they are assigned once the allocation process is completed. This information will be securely stored in a password-protected digital file. A duplicate file will be created on a hard drive to which only the lead researcher will have access. Once the baseline surveys have been completed, subject allocation will be conducted by a different member of the research team, who will not be involved in any other study-related tasks. This allocation will be based on a computer-generated random sequence obtained from a reputable source (https://www.randomizer.org). Participants will be assigned to either of these two groups: (1) AIR + Mindfulness group; (2) Control group based on relaxation therapy. Participants and psychotherapists conducting the interventions will not be blinded to the intervention condition for practical reasons. However, blinding will be maintained during the initial assessment (pre-intervention). Additionally, the research assistant responsible for sharing the assessment survey link will be blinded, as will the expert conducting the statistical analysis.

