### Interventions

Both groups will undergo active interventions consisting of eight two-hour weekly sessions, followed by one session per month as booster over the following three months. Each session will be conducted online. Furthermore, participants will receive homework assignments and audio files with practice exercises for use between sessions. Prior to commencement of the program and participant allocation, an informative online session will be held. During this session, participants will have the chance to address any concerns they might have about the study. They will have received the study information sheet and the informed consent in advance.

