### Outcomes

Data will be collected using a battery of self-reported questionnaires administered at baseline, after the intervention (post-intervention,) and at three-month follow-up. Outcomes of the AIR + Mindfulness and the relaxation conditions will be evaluated and compared. All variables and assessment periods of the study can be found in Table 3.

**Table 3 Tab3:** Study Outcomes

Instrument	Assessment Area	Time
Bespoke survey	Sociodemographic	Baseline
SF-36	Quality of life	Baseline, post-treatment and 3-month follow-up
SCPGS	Pain intensity	Baseline, post-treatment and 3-month follow-up
PCS	Catastrophizing	Baseline, post-treatment and 3-month follow-up
MFIS	Fatigue	Baseline, post-treatment and 3-month follow-up
ISI	Insomnia	Baseline, post-treatment and 3-month follow-up
GAD-7	Anxiety	Baseline, post-treatment and 3-month follow-up
PHQ-9	Depression	Baseline, post-treatment and 3-month follow-up
MEF-30	Memory	Baseline, post-treatment and 3-month follow-up
FFMQ-24	Mindfulness	Baseline, post-treatment and 3-month follow-up
ERQ	Emotion Regulation	Baseline, post-treatment and 3-month follow-up
AAQ-II	Experiential avoidance	Baseline, post-treatment and 3-month follow-up

SF-36, Short Form Health Survey; SCPGS, Spanish Chronic Pain Grading Scale; PCS, Pain Catastrophizing Scale; MFIS, Modified Fatigue Impact Scale; ISI, Insomnia Severity Index; GAD-7, General Anxiety Disorder; PHQ-9, Patient Health Questionnaire; MEF-30, Memory Failures of Everyday; FFMQ-24, Five Facet Mindfulness Questionnaire; ERQ, Emotion Regulation Questionnaire; AAQ-II, Acceptance and Action Questionnaire-II.

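### The one stated route for adverse effects depends on attending sessions and on an unblinded therapist, so it falls short of the study-long monitoring promised

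*Protocol article*

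**What the plan says.** All the statements are in the protocol article.

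- **Promise.** Data collection and monitoring: "Throughout the study, there will be careful monitoring for any potential adverse effects experienced by participants". The same sentence adds that "owing to the nature of the intervention programs, such effects are not expected to occur".
- **Route.** The next sentence reads: "Participants will be encouraged to promptly report any signs of worsening during sessions". If adverse effects arise, "the psychotherapist overseeing the intervention will report them to an independent data monitoring committee (IDMC").
- **Who reports.** Randomization, allocation, and blinding: "Participants and psychotherapists conducting the interventions will not be blinded to the intervention condition for practical reasons". The assistant who shares the survey link is blinded.
- **Contact schedule.** Interventions, for both arms: "eight two-hour weekly sessions, followed by one session per month as booster over the following three months". Homework and audio practice take place between sessions.
- **What is measured.** Outcomes: "All variables and assessment periods of the study can be found in Table 3". Table 3 lists SF-36, pain, fatigue, insomnia, anxiety, depression, memory and process scales at baseline, post-treatment and three months. It has no adverse-effect item.
- **Analysis.** The Data analysis plan names no tabulation of harms. Its Jacobson-Truax reliable-change analysis concerns improvement in quality of life.

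**The concern.** The section does not stay silent and leave the method to a fuller document. It makes a commitment covering the whole study, then states a method that depends on being in a session and on volunteering the problem. The people most likely to be missed are those who leave because they feel worse. The Discussion itself foresees dropout for health reasons.

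Two things are at stake. The IDMC can act only on what reaches it, and the stated path to it is the therapist delivering the treatment. A report by arm would also rest on unprompted complaints passed on by unblinded staff, with no common question stated for the two arms. A low count could then reflect weak capture as easily as few events.

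**Working it through.** The plan gives no figure for harms, so there is none to reproduce. The one figure that bears on the point is expected dropout.

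**Step 1: people outside the route.** Sample size gives 42 evaluable per arm, about 15% dropout, and 50 per arm randomised.
- Check of the plan's inflation: 42 / (1 − 0.15) = 49.4, rounded up to 50. This agrees.
- Expected dropouts: 0.15 × 50 = 7.5 per arm, so 0.15 × 100 = 15 in total.

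The 15 is a count of people beyond a session-based route after they leave, not a count of missed events. They can report while they still attend. It assumes that dropout from the study and stopping sessions coincide; the article gives no separate rate for stopping sessions.

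**Step 2: time outside the route.** Sessions run weekly for 8 weeks, then "followed by one session per month as booster over the following three months" (taken as about 13 weeks). The three-month follow-up is also about 13 weeks. The article does not settle whether post-treatment means after session 8 or after the last booster.
- After session 8: 8 + 13 = 21 weeks. The last 13 weeks contain three sessions, so the gaps are about a month.
- After the last booster: 8 + 13 + 13 = 34 weeks. The last 13 contain no session, and 13/34 = 38%.

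The sparse period differs between the two readings, but neither gives continuous coverage. The Abstract gives the follow-up as six months; the body, including Table 3, says three, and three is used here.

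**Step 3: what the wording covers.** The phrase *during sessions* can attach to the reporting or to the worsening. On the first reading, trouble between sessions is heard only if the person attends later and raises it. On the second, worsening during home practice is not covered at all.

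**Step 4: whether the surveys fill the gap.** They reach both arms alike, through a blinded assistant, and include PHQ-9, GAD-7, ISI, MFIS, the pain scale and SF-36. Deterioration on these can be compared between arms without the therapist. Three gaps remain:
- No text sends the answers to the IDMC.
- As listed, the scales do not record whether someone sought care or stopped sessions because of worsening.
- The article describes the survey contact as following completion of the assigned intervention, so it is not stated that people who stop early receive it.

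**Step 5: size of the under-count.** This needs a true rate of worsening and a capture rate in each arm. The documents give neither, so no figure is offered.

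**The case against.** The strongest reply is that this is a condensed article. It makes a general commitment and sets up a three-discipline IDMC, and it nowhere says that session reporting is the exclusive channel. Event forms and logs commonly sit in the full protocol. Table 3 is a table of outcome questionnaires, so the absence of an event log from it proves little. This stands in part: the point is about the only route *stated*. It does not remove the point, because the route that the article does state fails to meet the commitment made just before it.

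Several stronger readings are tempting, and the documents do not support them:

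- **People who leave have no way to report.** Research-team contact details are given at recruitment and participants receive email from the team. The article simply does not offer that contact as a route for adverse effects.
- **Harms cannot be compared between arms.** The session schedule is the same in both arms and the symptom scales are collected identically. Spontaneous counts can be compared; they would be incomplete and open to bias.
- **Arm is confounded with therapist.** Each programme is to be led by a psychologist with suitable training. The number of therapists, and whether they differ between arms, is not stated.
- **A fixed 38% of the study has no session.** That holds on only one of the two timelines.
- **Zero reports would be uninformative because of the route.** Zero events in 42 leaves an exact two-sided 95% upper limit of 1 − 0.025^(1/42) = 8.4%. That reflects sample size and would be the same after the fix.
- **The trial will declare the programme free of harm.** No such conclusion is planned.

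Prompted items also have a drawback. Long COVID symptoms fluctuate, so many reports will be background. A formal test of harms would be weak in any case: with 50 per arm and assumed rates of 5% versus 15%, power is about 38%; for 10% versus 20%, about 29%. The gain is in complete, like-for-like capture, not in a significance test.

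**Conclusion.** The concern holds in a limited form. The one stated route is spontaneous, tied to sessions and passed on by an unblinded therapist. It does not deliver the study-long monitoring promised in the same section. It leaves out people after they stop attending (about 15 of 100 if the expected dropout occurs and coincides with stopping sessions) and covers thinly the time between or after sessions. Adverse-effect counts by arm would be incomplete and open to differential reporting; the direction and size of any bias cannot be stated from the documents.

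This rests on reading the stated route as the operative one. If the full protocol already has prompted collection in both arms that also reaches those who stop, the remaining task is to correct the wording. The point is a cheap improvement and does not threaten the primary analysis.

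**What to change.** 1. Add a short adverse-effect and worsening item set to the existing online surveys at post-treatment and three months, with identical wording in both arms: any new or worsened symptom, how severe, whether care was sought, and whether sessions were stopped because of it.
2. Send it to every randomised participant, including those who stopped attending, through the blinded assistant who already shares the survey link.
3. Pass the answers to the IDMC by participant code, in addition to therapist reports.
4. Tabulate the answers by arm, descriptively.
5. In Data collection and monitoring, replace *during sessions* with *at any time, in or outside sessions*.

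The cost is a few survey items and a short amendment. The survey becomes slightly longer, and the IDMC will have more background Long COVID symptom reports to review. Participants still know their allocation when they answer, so the change removes dependence on the therapist but not all reporting bias.

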**Fig. 1 Fig1:**
[figure not shown]
Flowchart for the randomized clinical trial

### Interventions

Both groups will undergo active interventions consisting of eight two-hour weekly sessions, followed by one session per month as booster over the following three months. Each session will be conducted online. Furthermore, participants will receive homework assignments and audio files with practice exercises for use between sessions. Prior to commencement of the program and participant allocation, an informative online session will be held. During this session, participants will have the chance to address any concerns they might have about the study. They will have received the study information sheet and the informed consent in advance.

#### AIR + mindfulness

This intervention will consist of an AIR protocol combined with elements of mindfulness training. The psychotherapeutic approach of the AIR program focuses on enhancing coping skills and strategies for dealing with fear and stressful situations. This is hypothetically achieved by interrupting the amygdala’s conditioned anxiety or fear responses. The program consists of psychological techniques including breathing exercises, meditation exercises, generative practices, compassion practices, cognitive behavioral therapy, and neuro-linguistic programming. AIR is a therapy that was specifically designed to alleviate symptoms in patients with CFS and fibromyalgia [15, 16, 18–20]. Neurobiology studies have demonstrated that exposure to acute stress stimuli, trauma, or extended periods of stressful expectations (such as those that can arise from enduring a pandemic or experiencing Long COVID), can result in the development of a conditioned response in the amygdala to new stimuli [35, 36]. Once conditioning becomes established in the amygdala, any neutral stimulus that occurs in the presence of this “trauma” acquires the ability to elicit fear in the organism. It triggers unconscious “fight and flight” responses, as if there were a real threat. This process is also associated with neuroinflammation of the brain in patients with conditions like CFS and fibromyalgia [3]. Thus, the stress conditioning process of the amygdala enters into a loop with all the abovementioned mechanisms perpetuating themselves over time [18, 19].

The retraining intervention focuses on dismantling fear conditioning in the amygdala, which contributes to the bodily symptoms observed in the disease. This is achieved by progressively undoing the conditioning and mitigating heightened levels of nervous system stimulation through the following methodology: (a) repeatedly disrupting the established unconscious conditioning; (b) substituting these fear and threat-related messages with messages of bodily safety; and (c) strengthening the activity of the prefrontal cortex and reducing the over-activation of the amygdala through mindfulness. The incorporation of safety messages results in a transformation of the unconscious implications of amygdala conditioning.

Mindfulness training of is associated with increased cortical thickness in the anterior insula (involved in interoception, affected by fibromyalgia and chronic fatigue) and the frontal cortex (involved in the integration of emotions as fear and cognition process). Moreover, this technique seems to change cognitive evaluations of what is considered a threat, decrease reflective thinking, and reduce stress. Mindfulness can also directly increase positive states of arousal [37–39]. Thus, the practice of mindfulness seems to reinforce the AIR intervention, given that the activity of the amygdala has been seen to decrease with its practice, as well as activation of the prefrontal cortex, an area also involved in diminishing the fear conditioning response.

Previous studies suggest that the practice of mindfulness causes effective and lasting results for the symptomatology and underlying pathology of post-viral fatigue, such as Long COVID. It has been found to reduce fatigue and unrefreshing sleep, and for those with post-viral infections, to improve immunity and reduce pathogen-driven inflammation [40, 41].

The intervention will be administered by a clinical psychologist who is trained in and has experience in facilitating groups for both the AIR program and mindfulness-based interventions. The content of each session is described in Table 1.

**Table 1 Tab1:** AIR + Mindfulness program

Session 1	Overview of the retraining and mindfulness course. Introduction to the course. Goals. Work method. Developing a regular mindfulness practice. Mindfulness practices. Guidelines for the regulation of the nervous system. Thought diary. 3-minute mindfulness practice. Health visualization.
Session 2	Hypothesis on the origin of Long COVID. Theoretical aspects. The amygdala-insula-limbic hypothesis on how stress activates the nervous system. Conditioning and reconditioning, and health visualization. Breathing meditation.
Session 3	Main technique of reeducation of the amygdala and the insula. Reconditioning. Learning to break physical activations caused by stimuli and symptoms. Patterns, meanings, and unconscious negative emotions. Somatic responses in the body. Guidelines for establishing a daily practice. Body scan meditation.
Session 4	Attitudes with retraining: reducing stress and expectations during the intervention. Meanings and activation caused by the fear of failure in terms of recovery. Disidentification and acceptance of symptoms. Introduction to the work of subpersonalities. Awareness of personality traits. Mindfulness practice. Incorporation of informal practices into daily life. Walking meditation.
Session 5	Management of symptoms and related negative emotions. Disidentification and radical acceptance of symptoms. Resistance to symptoms. Lifestyle and pace to support retraining. How to pace yourself, sleep more soundly, expose yourself to daylight, healthy lifestyle and cope with crises. Smooth Flow Practice.
Session 6	The AIR accelerator technique. Retraining of repeated somatic signals, patterns, beliefs, behaviors related to persistent Covid disease. Disidentification of mental contents. Mindfulness practice. visual metaphors.
Session 7	Awareness of limiting beliefs related to the disease. How to identify and change them with tonsillar reeducation work. Motivation and meaning of life. Meditation on values.
Session 8	Cycles and stages of recovery and return to normal life. How to incorporate the tools into daily life as health improves. How to stay healthy in the long term. Positive visualizations of the future. Positive psychology. Exercise on gratitude. Cultivating positive emotions. Practice on Reconnecting with happiness. Protocol review and summary

#### Relaxation intervention

The program for the active control group includes progressive muscle relaxation training, as proposed by Bernstein and Borkovec [42], with the addition of visualization and breathing practices. The intervention will be administered by a clinical psychologist who is experienced with groups and is trained in relaxation therapy. The sessions contained in this program are described in Table 2.

**Table 2 Tab2:** Relaxation program

Session 1	Presentation of the group and the relaxation objectives. Basic principles of progressive muscle relaxation. Brief explanation of the initial procedure with 16 muscle groups. Progressive muscle relaxation practice with 16 muscle groups. Identifying the sensations of and difficulties with relaxation.
Session 2	Sharing homework-related experiences and doubts. Imagination training and visualization techniques. Practice of progressive muscle relaxation with 16 muscle groups. Identifying the sensations of and difficulties with relaxation.
Session 3	Sharing homework-related experiences and doubts. Brief explanation of the procedure with 7 muscle groups. Practice of progressive muscle relaxation with 7 muscle groups. Visualization practice: orange. Identifying the sensations of and difficulties with relaxation.
Session 4	Sharing homework-related experiences and doubts. Practice of progressive muscle relaxation with 7 muscle groups. Visualization practice: the beach. Identifying the sensations of and difficulties with relaxation.
Session 5	Sharing homework-related experiences and doubts. Brief explanation of the procedure with 4 muscle groups. Practice of progressive muscle relaxation with 4 muscle groups. Visualization practice: the landscape. Visualization practices: the globe. Identifying the sensations of and difficulties with relaxation.
Session 6	Sharing homework-related experiences and doubts. Brief explanation of relaxation by evocation, relaxation by evocation + counting, and relaxation by counting. Relaxation by evocation. Mental relaxation and visualization practice: the perfect day. Identifying the sensations of and difficulties with relaxation.
Session 7	Sharing homework-related experiences and doubts. Explanation of relaxation techniques through breathing. Breathing practice: count, lengthen, hold. Visualization: the ray of light. Identifying the sensations of and difficulties with relaxation.
Session 8	Sharing homework-related experiences and doubts. Explanation: bringing the practice to my daily life, maintenance of habits. Breathing practice. Practice 4 muscle groups. Display. Identifying the sensations of and difficulties with relaxation.

### Outcomes

Data will be collected using a battery of self-reported questionnaires administered at baseline, after the intervention (post-intervention,) and at three-month follow-up. Outcomes of the AIR + Mindfulness and the relaxation conditions will be evaluated and compared. All variables and assessment periods of the study can be found in Table 3.

**Table 3 Tab3:** Study Outcomes

Instrument	Assessment Area	Time
Bespoke survey	Sociodemographic	Baseline
SF-36	Quality of life	Baseline, post-treatment and 3-month follow-up
SCPGS	Pain intensity	Baseline, post-treatment and 3-month follow-up
PCS	Catastrophizing	Baseline, post-treatment and 3-month follow-up
MFIS	Fatigue	Baseline, post-treatment and 3-month follow-up
ISI	Insomnia	Baseline, post-treatment and 3-month follow-up
GAD-7	Anxiety	Baseline, post-treatment and 3-month follow-up
PHQ-9	Depression	Baseline, post-treatment and 3-month follow-up
MEF-30	Memory	Baseline, post-treatment and 3-month follow-up
FFMQ-24	Mindfulness	Baseline, post-treatment and 3-month follow-up
ERQ	Emotion Regulation	Baseline, post-treatment and 3-month follow-up
AAQ-II	Experiential avoidance	Baseline, post-treatment and 3-month follow-up

SF-36, Short Form Health Survey; SCPGS, Spanish Chronic Pain Grading Scale; PCS, Pain Catastrophizing Scale; MFIS, Modified Fatigue Impact Scale; ISI, Insomnia Severity Index; GAD-7, General Anxiety Disorder; PHQ-9, Patient Health Questionnaire; MEF-30, Memory Failures of Everyday; FFMQ-24, Five Facet Mindfulness Questionnaire; ERQ, Emotion Regulation Questionnaire; AAQ-II, Acceptance and Action Questionnaire-II.

